#### **F. Collection and testing of samples**

Four blood samples (ca. 5mL clotted blood) will be collected from each subject, at months 0, 2, 7 and 12 of the study. One extra blood sample (ca. 30mL heparinised blood) may be collected at month 7 i.e. one month following the final vaccine dose. An optional self-taken lower vaginal sponge will also be collected on month 7. Participation in the study will not depend on whether the individual volunteers to give a sponge sample.

Forms from appropriate Standard Operating Procedures (SOPs) will be included with samples to document the movement of samples between sites and laboratories. Logs of samples sent and received will be kept at Cfl to enable the identification of any lost or delayed samples and provide a log of where samples are currently stored. Laboratory staff will be blinded to the vaccine received.

#### **Blood**

Blood sampling will be in accordance with venepuncture SOP. No more than two attempts at venepuncture will be made. An anaesthetic cream (EMLA or Ametop) will be offered for use on the intended bleeding site to minimise discomfort. At least 5ml of blood and no more than 10 ml of blood will be taken at each sample collection point for serum generation. At month 7 (one month following the full regimen of GardasilTM or CervarixTM doses) an additional 30mls of

heparinised blood may be taken for the isolation and storage of peripheral blood mononuclear cells (PBMC; white blood cells).

The Vaccine Research Nurse (VRN) will stick an adhesive label bearing the subject's unique number onto each sample tube. She will also write the subject's initials on each label. Adhesive labels bearing the subject number will be packed with the samples and sent to the primary receiving laboratory, which will be:

**Centre for Infections**

**Health Protection Agency**

**[name]**

**[name]**

VRNs will send standard 5mL blood samples taken at **Months 0, 2, and 12** by Royal Mail next day delivery. Blood samples taken at **Month 7** (standard 5mL blood plus 30mL heparinised blood) will be sent by courier for same day or overnight delivery, as appropriate.

Blood will be processed and tested or archived according to laboratory SOPs for measurement of the following:

- i. HPV antibodies using binding and functional assays
- ii. HPV cell mediated immune responses

**(Optional) Lower Vaginal Self-Taken Sponge**

A self-taken lower vaginal sponge will be collected at **Month 7** and sent by courier with the **Month 7** blood samples, as above, if applicable. This sample is voluntary and refusal to take part will not affect further participation in the study. Instructions on how to take the sponge will be given by the Vaccine Research Nurse. Essentially, a sterile sponge is inserted 1-2cm into the lower entrance of the vagina, and the sides of the vagina are sponged. The sponge is then placed into transport medium and labelled with an identification sticker. These samples will be tested for HPV-specific antibodies generated to the vaccine.

On completion of testing, samples will be archived at the Health Protection Agency, Colindale, where permission for this has been granted by the subject.

**I. Collection of safety data**

Subjects will be asked to record daily in a health diary any local reaction (redness, swelling, tenderness) and give measurements if present, to take their temperature using a thermometer provided. They will be asked to record any visits to a doctor – hospital or GP – as well as to document anything else that they think study personnel should be aware of.

**H. Data records**

Vaccine Research Nurses (VRNs) will maintain their own records of all subjects enrolled in the study under their care. Information kept will include the surgery or school attended, vaccination due dates, contact details.

CRFs will be provided to VRNs by Cfl. CRFs will be numbered and will indicate the group to which the subject assigned that number has been randomised. Subjects will not be made aware of this information. CRF packs will comprise a series of cards relating to each clinical stage of the study process. Also included will be a change of circumstances card for any

subject whose name or address is altered during the course of their participation, and a completion card that will detail whether the protocol was completed or whether subjects were withdrawn or lost to follow-up, with appropriate details given.

VRNs will complete the CRFs at each visit and these will be sent to Cfl. A study database will be constructed at Cfl to record the information collected in the CRFs. As the data is being entered, the CRFs will be monitored for completion errors or omissions. When such a problem is identified the card will be photocopied and the field for correction marked. The photocopy will be sent to the VRN who will make the correction, crossing out any incorrect information with a single line, and will sign and date the change. On return of the photocopy to Cfl the database will be updated accordingly and the photocopy filed with the original CRF.

Information from the clinical record cards will be entered at Cfl into a database on a microcomputer. Data will be entered twice by two independent data-entry staff and will be verified electronically. Laboratory data will be e-mailed to the Consultant for Clinical Trials and imported into the database so that test results can be linked to clinical records.

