## CONDUCT OF THE STUDY

### A. Recruitment

Recruitment will be conducted through schools and general practitioners.

General practitioners will be approached to agree to the participation of their surgery in the study and will be asked to document their agreement to the study being conducted in their surgery by the completion of a protocol approval form (Appendix 6). No subjects will be recruited from a surgery until this has been obtained. A site file will be provided to each participating surgery, with documents as listed in the index (Appendix 4). Study investigators and co-ordinators will be available to contact should health professionals or parents require any further information.

Subjects will be recruited from general practices in Hertfordshire and Gloucestershire. Recruitment and follow up will be by dedicated Vaccine Research Nurses (VRNs) currently employed by the Health Protection Agency.

For school-based recruitment, school staff will identify potential participants based solely on age and gender and give/send the initial invitation to participate both to the girl and a parent/guardian. Only girls returning forms requesting further information about the study will be contacted by the Vaccine Research Nurses and contact numbers will be provided for parents and students who require further information about the study. As well as the approved study information leaflet families will be provided with the standard Department of Health information about HPV vaccination and will have the opportunity to discuss the study with dedicated Vaccine Research Nurses and / or medical staff should they wish to do so. Information will be provided in a timely manner to ensure parents/participants have time to seek the opinion of others, should they wish, such as family, friends and other health professionals. Schools will decide the most appropriate methods for identifying potential participants from their registered pupils. It is anticipated that this will almost invariably be via a computerised search of registered female pupils of eligible age.

Written information will be provided about the study and clinicians will discuss the study with individuals and answer any questions before obtaining written informed consent for participation for those who wish to enrol. Because subjects will be under 16 years of age, the *patient information leaflet* will encourage informed discussion of the study with a parent or guardian.

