Following confirmation of inclusion and exclusion criteria, subjects will be enrolled in the study and will be allocated to one of the two treatment groups by a randomisation procedure – see below. No study procedure will be undertaken until written informed consent is given by a parent or guardian and the inclusion/exclusion criteria are verified.

GPs will be informed of the participation of each subject in the study by a letter (please see Appendix 1). Provision of this information forms part of the consent procedure.

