#### **E. Randomisation**

A computerised block randomisation list will be produced by the Statistician at Cfl. Each VRN will be allocated blocks of sequential numbers in accordance with the block size used for randomisation. On recruitment to the study, each subject will be allocated, in order of inclusion, the next available study number by their VRN. The study number will define the group to which the subject is assigned and therefore the vaccine they will receive. Vaccinated individuals, however, will not be aware of which HPV vaccine (GardasilTM or CervarixTM) they will be receiving during the course of the study. Laboratory staff will be aware of the study number and patient initials associated with the collected samples but will not be able to link these data with the vaccine received nor other patient identifiers.

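### Allocation is not concealed from the recruiting nurse, who can know the next vaccine before she decides when or in what order to enrol a girl

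*Protocol*

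**What the plan says.** Protocol section A (Recruitment) makes the nurses the recruiters: "Recruitment and follow up will be by dedicated Vaccine Research Nurses (VRNs) currently employed by the Health Protection Agency". It puts the eligibility check before enrolment and allocation: "Following confirmation of inclusion and exclusion criteria, subjects will be enrolled in the study". It also requires a parent's or guardian's written consent before any study procedure.

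Section E (Randomisation) describes the sequence and its use:

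- "A computerised block randomisation list will be produced by the Statistician at Cfl". No block size is given.
- "Each VRN will be allocated blocks of sequential numbers in accordance with the block size used for randomisation".
- On recruitment, "each subject will be allocated, in order of inclusion, the next available study number by their VRN".
- That number fixes her group, and with it her vaccine.

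Section H (Data records) adds that "CRFs will be provided to VRNs by Cfl" and that "CRFs will be numbered and will indicate the group to which the subject assigned that number has been randomised". Only subjects are said there to be kept unaware of the group.

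Elsewhere, laboratory staff are blinded (sections E and F), and GPs learn which vaccine was given only after the month 12 blood sample (section D). No section describes sealed packs, central or telephone release, or any other step that hides the next group from the nurse.

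**The concern.** Randomisation protects the comparison only if the person who enrols cannot foresee the next assignment. Here one person recruits, holds the numbers in sequence, assigns the next one, and is supplied with numbered forms that show the group. She could, consciously or not, bring one enrolment forward, hold another back, or change the order in which two girls enter. If those choices are related to immune response, the arms differ before the first dose. A blinded assay then measures that difference faithfully and does not remove it.

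What is at stake is the comparison of the two vaccines. It is objective (ii), and the sample size section sizes it at the 5% level. Selection on characteristics that are not recorded cannot be adjusted for afterwards.

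**Working it through.** **1. Who can see what, and when**

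| Step | Protocol section | Consequence |
|---|---|---|
| VRNs recruit | A | The recruiter is the nurse |
| Each VRN holds whole blocks of sequential numbers | E | She knows which number comes next |
| She gives out the next unused number, which fixes the vaccine | E | Number and vaccine are equivalent |
| She is supplied with numbered CRFs showing the group | H | She can read the vaccine for that number |
| Group withheld from subjects, laboratory staff and, until month 12, GPs | D, E, F, H | The recruiter is not among those shielded |

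If the marked forms are at hand before enrolment, the next assignment is 100% predictable.

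**2. Would removing the mark from the CRF be enough?**

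The nurse gives the vaccine herself (section D), and the trial labels must leave the supplier's batch and expiry information readable (section B). She therefore learns each past allocation in her own blocks. Suppose she also knows the block size, and guesses whichever vaccine has more places left in the current block.

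- Block of 2: the chances of a correct guess are 1/2 and then 1. The average is (0.5 + 1)/2 = 75%. One place in two is certain: 50%.
- Block of 4: the chances at the four places are 1/2, 2/3, 2/3 and 1. The average is 2.833/4 = 71%. The third place is certain with probability 1/3 and the fourth always, so (1/3 + 1)/4 = 33% are certain.

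The same enumeration for larger blocks gives:

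| Block size (assumed) | Best-guess accuracy | Known with certainty |
|---|---|---|
| 2 | 75% | 50% |
| 4 | 71% | 33% |
| 6 | 68% | 25% |
| 8 | 67% | 20% |
| 10 | 65% | 17% |

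So the blocks are a second, weaker route to prediction.

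**3. The plan's own sample size**

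For the ten pairs of percentages in the sample size table, the two-proportion formula with continuity correction (two-sided 5%, 80% power, 1:1) gives 201 to 202 per arm. The plan's 200 per arm is reproduced, and this point does not change it.

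**4. What a shift would do to the test**

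Inputs: 200 per arm (sample size section); 50% response in both arms (assumed, and one of the rows in the plan's table); two-sided 5% test (two-sidedness assumed, because the table gives limits on both sides); shift d in one arm's proportion caused by selection (assumed).

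Standard error of the difference = √(2 × 0.5 × 0.5 / 200) = 0.05.

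Type I error = Φ(−1.96 + d/0.05) + Φ(−1.96 − d/0.05).

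| d | d/0.05 | First term | Second term | Type I error |
|---|---|---|---|---|
| 0.02 | 0.4 | Φ(−1.56) = 0.059 | Φ(−2.36) = 0.009 | 6.9% |
| 0.03 | 0.6 | Φ(−1.36) = 0.087 | Φ(−2.56) = 0.005 | 9.2% |
| 0.05 | 1.0 | Φ(−0.96) = 0.169 | Φ(−2.96) = 0.002 | 17.0% |

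These figures show how sensitive the test is. Nothing in the protocol says how large d would be.

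**The case against.** A reader might infer that the nurses do know each girl's vaccine before enrolling her. The protocol does not say that. It does not say when the CRF packs reach the nurse or whether the mark can be seen on an unopened pack. What stands is that she can know, because numbers are handed out in advance, marked forms are supplied to her, and nothing prevents prior access.

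Consent and eligibility do come before allocation. That order governs the paperwork. It does not hide the next number from a nurse who is deciding when to complete that paperwork.

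The nurse's discretion is narrower than it might seem. On the school route, school staff identify girls by age and sex alone, and nurses contact only those who return a form. Medical staff may also talk to families. This limits whom she approaches, but it leaves the timing and order of enrolment with her.

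The laboratory is blinded and the main outcome is an assay result. This limits bias in measurement, not selection at entry.

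The likely routes to a difference are not strong. Ages run only from 12 to 15 years, and the eligibility section assumes that response does not differ from that of girls aged 12 to 13. The protocol mentions no parental preference between vaccines. These points make a large shift less likely, but they do not rule one out.

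The type I error figures rest on invented shifts. They also bear only on the comparison between vaccines, since the main outcome is a proportion with an exact confidence interval. Both points are right, and the figures should be read in that way.

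**Conclusion.** The point holds. As the protocol is written, allocation is not concealed from the person who recruits, and the comparison between vaccines is open to selection bias of unknown size. This rests on the text of sections A, E and H and on the absence of any concealing step.

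The documents do not show that any nurse used such knowledge, that the arms differ, or that the type I error is 7%, 9% or 17%. Those values follow only if shifts of 2, 3 or 5 points are assumed at 50% response. The block predictions likewise assume a block size, and a nurse who knows it, because the protocol gives no size and does not say that nurses are told it.

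The matter should be put right despite the unknown size. It affects the validity of the randomised comparison, analysis cannot reliably repair it, and the remedy is cheap.

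**What to change.** The target dates say that recruitment has started, so apply the change to all unused numbers.

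1. Take the group off the CRF pack as supplied to the nurse.
2. Put the group in a sequentially numbered, sealed opaque envelope. Open it only after consent and eligibility are signed and the girl's details are written on it.
3. After opening, record the group in the CRF, because the nurse needs it at the later vaccination visits.
4. Regenerate the list for the unused numbers with randomly varying block sizes that are not disclosed to the nurses. This deals with prediction from vaccines already given.
5. Compare baseline age and month 0 antibody by arm, separately for girls enrolled before and after the change. Month 0 blood is already taken from every girl. A balanced result would be reassuring but would not exclude selection on unrecorded factors.

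The cost is a set of envelopes, a regenerated list, and both vaccines to hand at each enrolment. No extra subjects or staff are needed, and the sample size does not change.

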## **STATISTICAL METHODS**

Full details will be given in the statistical analysis plan produced by the Statistician.

### **Brief description.**

The primary purpose of this study is to determine the level of neutralising antibody reactivity (i.e. antibodies able to prevent HPV infection of target cells in laboratory culture) against not only the vaccine-incorporated types (HPV 16 and 18) but also the genetically-related, non-vaccine cancer-causing types (31, 33, 35, 39, 45, 52, 58, 59, 68). The main outcome will be the proportion of vaccinated individuals generating measurable antibody-mediated neutralisation against HPV 45 at the peak response (one month post-3rd dose; i.e. month 7). Further outcome measures will be the proportion of vaccinated individuals generating measurable antibody-mediated neutralisation against non-vaccine HR HPV types and the geometric mean titres for each HPV type, by vaccine and sample type, at each time point. For proportions exact confidence intervals will be calculated. For titres data will be logged (base 10) and assuming normality on the log-scale 95% confidence intervals calculated. If for any reason data are clearly not normal then the 95% confidence interval may be calculated after excluding outliers (such as those individuals who fail to generate an acceptable immune response to vaccine-incorporated HPV types, 16 and 18). If a large proportion of the subjects fail to generate an acceptable response then it may not be possible to calculate geometric means.

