## 1. BACKGROUND AND RATIONALE

Cervical screening (the 'smear test') helps prevent cervical cancer by finding early signs of abnormalities that can be addressed before they progress to cancer. Another way to prevent disease is to block infection by the human papillomavirus (HPV) types that can lead, usually after many years, to the development of cervical cancer. There are two vaccines now approved for use in many countries worldwide, including the UK: Cervarix™ (GlaxoSmithKline; GSK) and Gardasil™ (Merck).

The UK introduced HPV immunisation for girls in September 2008 using the HPV vaccine Cervarix™. The routine programme will target 12-13 year old girls and there will be a catch-up programme for girls up to 18 years. The first cohort to be immunised are girls born between 1st September 1995 and 31st August 1996 (current school year 8). Immunisation consists of a three-dose schedule over a six month period, starting in Autumn 2008. A schools-based programme has been recommended. The catch-up programme will target all girls born between 1st September 1990 and 31st August 1991 (current school year 13) alongside the first routine cohort (starting in Autumn 2008). The remaining catch-up years will be offered HPV vaccine from September 2009. The Joint Committee for Vaccination and Immunisation (JCVI) advised that a catch-up campaign for all women aged 18 years and over was not cost effective, but that HPV immunisation may be of benefit to individual women and further advice regarding this is anticipated from the Department of Health.

There are many types of HPV virus, some of which are cancer-causing (oncogenic). Both the vaccines (Cervarix™ or Gardasil™) should protect women against two of the most common oncogenic HPV types, 16 and 18, which account for about 70% of cervical cancer. However, as there are many other HPV types that also cause cervical cancer it will be necessary to maintain the cervical cancer screening programme. This is a significant recurrent investment by the NHS to protect the UK population from this devastating disease.

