## **SUBJECT ELIGIBILITY**

Inclusion criteria:

- Aged between 12 and 15 years at the time of the first immunisation
- Female
- No contraindications to vaccination as specified in the “Green Book” – Immunisation Against Infectious Disease, HMSO.
- Written informed consent obtained from parent or guardian of subject

Exclusion criteria

- Pregnant or become pregnant during the course of the trial (no contraindications to vaccination for those taking the contraceptive pill).
- Breast-feeding mothers
- Allergic to vaccine components

Deferral

- Subjects who have a fever (axillary temperature  $\geq 38^{\circ}\text{C}$ ), or have an acute infection will have injection delayed until resolution
- Not recommended in patients undergoing immunosuppressive therapy
- Not recommended for persons already undergoing vaccination as effect of co-immunisation with other vaccines has not been rigorously tested
- The JCVI (17 Oct 2007, 18 Jul 2008) advises that HPV vaccines and the Td/IPV school leaver booster (low dose diphtheria, tetanus and inactivated polio: Td/IPV) can be co-administered

Withdrawal criteria

- Subject becomes pregnant
- Subject or parent/guardian withdraws consent or lost to follow-up (HPA's SOP on Premature Withdrawal from a Study will be followed).

Girls aged 12 to 15 years will be recruited to this study. It is assumed that the immune response of these girls will not differ from that of girls vaccinated age 12-13 years as part of the routine HPV vaccination.

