### **TARGET DATES**

Recruitment started in September 2009 and is anticipated to end in autumn 2010. The final dose of the vaccine (Month 6) will be given spring 2010. The trial will last 12 months. The final samples are expected to be collected between autumn 2011.

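### The main outcome sets no month-0 condition, so a girl with HPV 45 neutralisation before dose 1 counts as a responder; defining it among month-0 negatives costs almost nothing

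*Protocol*

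**What the plan says.** Under Statistical Methods, Brief description, the main outcome is the share of vaccinated girls who generate measurable HPV 45 neutralisation, taken "at the peak response (one month post-3rd dose; i.e. month 7"). No month-0 criterion, rise from baseline or baseline adjustment is attached. The Sample Size Calculation uses the same quantity: its assumed rates, precision table and detectable-difference table all concern the share of month-7 samples that cross-react.

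The baseline information is collected. Section F states: "Four blood samples (ca. 5mL clotted blood) will be collected from each subject, at months 0, 2, 7 and 12 of the study". The further outcomes include "the geometric mean titres for each HPV type, by vaccine and sample type, at each time point", which takes in month 0.

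Subject Eligibility admits girls "Aged between 12 and 15 years at the time of the first immunisation". Neither prior HPV vaccination nor HPV serostatus appears among the exclusions. The nearest item, a deferral note on persons who are already being vaccinated, is about giving other vaccines at the same time.

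On timing, Background and Rationale says "The first cohort to be immunised are girls born between 1st September 1995 and 31st August 1996", with three doses from autumn 2008, and that the remaining catch-up years would be offered vaccine from September 2009. Target Dates says "Recruitment started in September 2009 and is anticipated to end in autumn 2010".

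**The concern.** The outcome is meant to measure cross-neutralisation induced by the study vaccine. A girl who already neutralises HPV 45 at month 0, and still does at month 7, satisfies the definition whatever the study vaccine did.

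The protocol's own dates make such girls possible. The first routine cohort was aged 13 to 14 in September 2009, inside the 12-15 window, and had been offered a full Cervarix course the year before. The protocol expects 25% to 90% of post-vaccination samples to react to HPV 45.

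Two things are at stake. The single-arm percentages, which are results in their own right with a stated precision, would be too high. The between-vaccine difference would be too small, with less power to detect it.

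**Working it through.** **Inputs from the protocol.** 200 girls per arm; 5% significance level (sidedness not stated; two-sided reproduces the table); 80% power; assumed HPV 45 positivity 25% to 90%; detectable pairs such as 50% v 35.7%, 25% v 13.5% and 90% v 79.5%.

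**Input not in the protocol.** The fraction f positive for HPV 45 at month 0. It is assumed equal in the arms, as randomisation leads one to expect, and assumed to persist to month 7. It is varied from 0 to 10%.

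**Step 1: reproduce the stated figures.** Precision is 1.96 × √(p(1-p)/200). This gives 4.2 points at 10%, 6.9 at 55%, 6.0 at 25% and 4.2 at 90%, matching the table.

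Power uses the two-proportion test with continuity correction:

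power = Φ{[|p1-p2| - 1/n - 1.96 × √(2p̄(1-p̄)/n)] / √((p1(1-p1)+p2(1-p2))/n)}, where p̄ is the mean of p1 and p2.

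For 50% v 35.7% and n=200: (0.143 - 0.005 - 1.96 × 0.0495)/0.0490 = 0.837, so power is 79.9%. All ten pairs give 79.7% to 80.0%. The protocol's figures are sound.

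**Step 2: add month-0 positives.** The observed proportion is f + (1-f)p. Each arm therefore rises by f(1-p), and the difference becomes (1-f)(p1-p2).

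- 50% v 35.7%, f=10%: 0.10 + 0.90 × 0.50 = 55.0% and 0.10 + 0.90 × 0.357 = 42.1%. The difference is 12.9 points instead of 14.3.
- One arm at a true 25%: the rise is 0.02 × 0.75 = 1.5 points at f=2% and 0.10 × 0.75 = 7.5 points at f=10%, against a stated precision of about ±6.
- One arm at a true 90%: f=10% adds 0.10 × 0.10 = 1.0 point, against a stated precision of about ±4.

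**Step 3: compare the two definitions.** All subjects uses n=200 per arm and the diluted rates. Month-0 negatives uses n=200(1-f) per arm and the undiluted rates.

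| True rates | f | All subjects, power | Month-0 negatives, power |
|---|---|---|---|
| 50% v 35.7% | 0 | 79.9% | 79.9% |
| | 2% | 77.9% | 79.0% |
| | 5% | 75.0% | 77.7% |
| | 10% | 69.8% | 75.2% |
| 25% v 13.5% | 0 | 79.9% | 79.9% |
| | 2% | 75.7% | 79.0% |
| | 5% | 69.5% | 77.7% |
| | 10% | 60.0% | 75.2% |
| 90% v 79.5% | 10% | 74.1% | 74.9% |

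At the low rates the protocol allows for HPV 31, a further outcome, the gain is larger: for 10% v 2.7% at f=2%, power is 67.9% in all subjects and 79.0% in month-0 negatives. In none of these cases does the restriction lose power relative to all subjects, because removing the dilution is worth at least as much as the girls removed.

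**The case against.** The protocol nowhere says that month-0 positives are to be counted as responders. Its wording about individuals generating neutralisation can be read as newly induced response. The passage is labelled a brief description, and "Full details will be given in the statistical analysis plan produced by the Statistician"; that plan is not at hand and may handle baseline. This stands in part: silence is not a rule. But the protocol fixes the main outcome itself and sizes the trial on plain month-7 positivity, so the operational reading has no baseline condition. A later restriction would change the stated outcome.

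It is also fair that f is unknown, that at f of 1% to 2% the effect on 50% v 35.7% is about one point of power, and that at high response rates it is negligible. All of that stands.

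Four stronger readings are tempting, and the documents do not support them:

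- **The month-0 sample is ignored.** Titres are planned at every time point, so baseline positivity would be visible.
- **The comparison is biased toward one vaccine.** Under randomisation, month-0 positivity is expected to be equal in the arms; the effect is dilution.
- **Previously vaccinated girls were enrolled.** The dates show that some age-eligible girls had been offered vaccine, not that any joined.
- **Restricting to month-0 negatives solves prior vaccination.** On the protocol's 25% to 90% range, 100-90 = 10% to 100-25 = 75% of previously vaccinated girls could be HPV 45 negative and would remain in the denominator.

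**Conclusion.** The point holds as a weakness in how the main outcome is defined. As written, a girl positive for HPV 45 before dose 1 counts as a responder, although the sample that would identify her is taken from everyone. No figure in the protocol is wrong.

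The size depends on f, which the protocol does not give, and on f being equal in the arms and persisting to month 7. Near f=0 the effect is negligible. It becomes material at about 5% to 10% when response rates are low to moderate. The single-arm estimates are then biased upward and the comparison loses power. The change is worth making because it was no worse for power in any case computed and uses data already collected.

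**What to change.** In Statistical Methods, define the main outcome as measurable HPV 45 neutralisation at month 7 among girls with none measurable at month 0. Apply the same type-specific rule to the other non-vaccine types. Report the month-7 proportion in all randomised girls as a sensitivity analysis, and adjust comparisons of log10 titre for the month-0 log10 titre. Use the same definition in the sample size text.

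The cost is a change of wording and a denominator smaller by the number of month-0 positives. No extra sample is needed; month-0 testing is already implied by the planned titres at each time point. Because the restriction rests on a baseline value, it keeps the randomised comparison within the month-0 negatives.

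Whether previously vaccinated girls may enrol is a separate eligibility question, which this change does not settle and the protocol should state.
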